## STUDY OVERVIEW

**DESIGN:** A comparative trial that compares two implementation models for integrating antidepressant treatment into HIV care within 10 health care facilities in Uganda. Using a cluster randomization, 5 clinics are assigned to implement a protocolized model, and 5 others rely on the clinical acumen of trained providers. To evaluate the models, data will be collected from documentation mechanisms integrated into routine care, and from random samples of 100-150 patients enrolled at each site that screen positive for possible depression and are followed for 12 months. A cohort of providers will also be enrolled at each site and followed over 24 months. We will compare the two models on uptake of antidepressant treatment, and change in depression (treatment response), as well as other quality of care outcomes.

**STUDY SITES:** Of the 10 healthcare facilities participating in the study, eight are run by the Ministry of Health and two are private, faith-based, not-for-profit healthcare facilities; two are district hospitals and the others are designated as health centre III or IV facilities by the Uganda Ministry of Health, and are located in the districts of Mpigi, Mityana, Luweero, and Wakiso.

**SAMPLE SIZE:** 10 clusters (clinics), with 100-150 patients at each clinic.

**POPULATION:** Over the course of 12 months at each site, research coordinators (Masters level graduates with social science training) will recruit random samples of 100-150 patients who the triage personnel screen as positive for potential depression (PHQ-2 > 2), who are confirmed to be positive in the research coordinator's own PHQ-2 administration, and who are determined to be medically stable.

**STRATIFICATION:** To ensure the two study arms are balanced on size of clientele (small clinics serve 300-1000 clients, while larger clinics serve 1500-3000 clients), which could influence depression care processes, randomization will be conducted within pairs of clinics that were matched on this variable.

**INTERVENTION:** The trial is comparing two active task-shifting implementation models of depression care: a *protocolized model* in which care is provided largely by trained nurses who act as depression care managers, and a model that relies on the *clinical acumen* of trained primary care providers (most, but not all, of whom are nurses as well). An alternative approach to the use of a structured protocol to guide depression care by non-mental health professionals, the clinical acumen model (like the protocolized model) takes an active approach to depression care by integrating a brief routine depression screening process for all patients at each clinic visit, but what the primary care provider does with this screening information is up to their discretion as opposed to following a structured protocol.

**PRIMARY OBJECTIVES:** The objectives of INDEPTH-Uganda are to compare the two task-shifting models on (1) reach (screening and follow-up rates), adoption (treatment uptake), fidelity (quality of depression care implementation by the providers), and effectiveness (alleviation of depression symptoms) implementation parameters. A secondary objective is to assess the impact of depression treatment on key economic (work) and public health (ART adherence, condom use) outcomes.

**IRB approval:** The study protocol has been approved by Institutional Review Boards at RAND Corporation (protocol # 2012-0115), Mildmay Uganda, and the Uganda National Council for Science and Technology.

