## 4.0 STUDY SETTING

The study is being conducted in collaboration with Mildmay Uganda, a non-government organization that provides holistic outpatient HIV care at its own clinics, trains healthcare workers throughout Uganda and the region, and provides technical assistance in HIV care to healthcare facilities across Uganda. Of the 10 healthcare facilities participating in the study, eight are run by the Ministry of Health and two are private, faith-based, not-for-profit healthcare facilities; two are district hospitals and the others are designated as health centre III or IV facilities by the Uganda Ministry of Health, and are located in the districts of Mpigi, Mityana, Luweero, and Wakiso. Each facility is a hospital that operates an HIV clinic on specific designated days of the week, and it is in these clinics that depression care is being integrated as part of this study. The 6 larger clinics operate 2-3 days per week and generally have 1 clinical or medical officer and 3 to 5 nurses to provide primary HIV care to a clientele ranging from 1500-3000 clients and 80-120 patients are seen each clinic day. The 4 smaller clinics operate one day per week and are manned by 1 clinical or medical officer and 2-3 nurses; client base ranges from 350-1000, with 40-60 patients seen each day.

Consistent with task-shifting approaches becoming increasingly common in the context of ART scale-up across the region, at all sites nurses serve as primary care providers (along with the clinical/medical officers), and manage the prescription and monitoring of ART and other common HIV medications; more complex conditions or complications that arise are typically managed by the clinical/medical officer. All clinics have expert clients (volunteer experienced HIV clients who display exemplary HIV care adherence and are trained to provide peer support and assist in lower level tasks) and village health team (VHT) workers (community lay volunteers) who volunteer to take on tasks such as triage assessments, filing and retrieving charts, and keeping the clinic clean. No psychiatric or depression care services were being

provided at these clinics prior to the study; clients who developed significant psychiatric symptoms are referred to the nearest district or regional hospital for care.

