**Longitudinal client cohort:** The client research participants will be assessed at baseline and months 6 and 12. The surveys will be administered by the research coordinator using computer assisted personal interview technology, and will include the PHQ-9 (to independently assess the presence of depression) as well as measures of demographic and background characteristics,

work activity, clinical appointment and ART adherence, quality of life, sexual behavior and measures of psychosocial functioning. All measures have been used successfully in our prior research in Uganda and have been translated into Luganda, the primary native language used in the study setting. Participants will receive 10,000 Ush (~\$4 USD) for each assessment.

**Longitudinal provider cohort:** The provider cohort will be surveyed at the start of intervention implementation and then at months 6, 12 and 24. The measures will include perceived competency in providing depression care, quality of depression treatment provided, effects of the treatment model on clinic functioning, provider burden and patient flow, and impact of depression treatment on the patient's quality of life.

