## 9.2 Statistical Analysis

The analyses must account for clustering of the data, unless the only comparisons are of cluster means or proportions, using clinic as the unit of analysis. For most outcomes we will perform such an analysis first, using standard t-tests or, where the observations per clinic vary, t-tests weighted by cluster-size. However, relative to individual level analysis this approach is limited by low power (low number of clusters); inflexibility in adjusting for baseline individual level covariates; and inability to model direct impacts of patient characteristics and their interactions with treatment. Therefore we will use regression methods on individual level data for most analyses, and the discussion below is largely restricted to these approaches. While such methods can directly model correlations among units in a cluster (random effects or multilevel models) or more simply adjust standard errors for clustering (GEE, robust standard errors), these approaches are not reliable when number of clusters is small: reliably estimating the ICC to adjust standard errors typically requires 20 or more clusters. Hence, we'll use standard regression methods, but rather than attempt to estimate ICC directly, we will explore the sensitivity of significance levels and conclusions to a range of plausible ICCs values for the outcomes.

AIMs 1a: Depression Treatment Uptake: We'll use logistic regression to compare the proportions of depressed patients (according to PHQ-2) receiving depression treatment in task-shifting vs. control arms. We expect that most patients whose PHQ-2 screen is followed up with a formal evaluation and diagnosis of depression will be prescribed antidepressants, so we are not examining this variable separately from treatment uptake; also, it would be difficult to ascertain if the doctor performed a formal evaluation in the standard arm. The treatment uptake outcome will be estimated using covariates to adjust for baseline characteristics such as age, sex, and physical health. We will add interactions of these covariates with study arm to assess which types of patients are likely to be diagnosed and treated in the task-shifting vs. standard models. For example, it is possible that nurses, who are largely female, are more likely to recognize and treat depression in female clients.

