AIM 1b: Change in Depression (treatment response): The effect of task-shifting on treatment response (change in PHQ-9) will be examined using an ITT approach and the whole sample. We will use a repeated-measures, mixed-model approach allowing for correlation of errors over time for an individual (for which the sample size of our individual level data is adequate). The model has the following form:

$$(1) \text{Depression}_{it} = \alpha + \beta(\text{treatment model})_i + \gamma(t) + \delta(\text{treatment model})_i(t) + \theta_i + \varepsilon_{it}$$

Where *t* is time period,  $\beta$  controls for baseline differences between the two,  $\gamma$  is the trend in the outcome common to both groups, and  $\delta$  is the interaction of treatment model with time and shows the intervention effect (task-shifting relative to the control).  $\theta_i$  is an individual random effect and  $\varepsilon_{it}$  idiosyncratic period specific error. A vector of individual level covariates  $X_i$  will be added to estimate the effects of patient characteristics and interactions of  $X_i$  and task-shifting will be used to test for moderators: e.g., do effects of the task shifting model vary by the patient's physical health at baseline? As this is ITT, the estimates will capture the average benefit for depressed PLHA, including those who do and do not receive antidepressant treatment.

To assess effects on those receiving antidepressants, we will estimate (1) on the sample of those treated in both arms; however, randomization does not ensure equivalence of the two groups, since the process of selection into diagnosis and treatment will likely differ. In particular we might expect more seriously depressed patients to be treated in the standard arm. This can be addressed by including baseline PHQ-9 in the regression, or with fewer parametric assumptions, using propensity score matching to match similar patients in control and treatment arms. As both approaches assume that observables fully control for differences across arms in relevant characteristics of treated patients, more caution will be needed in interpretation of the results.

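### Clinics are randomised in pairs matched on size, but no stated analysis uses pair or size, and Aim 1b model (1) uses baseline PHQ-9 only as an outcome

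*Protocol*

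**What the plan says.** **Design.** The Study Overview (Stratification) gives clientele size as the matching variable, a factor "which could influence depression care processes", and states that "randomization will be conducted within pairs of clinics that were matched on this variable". Allocation is 5 against 5: "5 clinics are assigned to implement a protocolized model, and 5 others rely on the clinical acumen of trained providers". Section 4.0 gives the split by size: "The 6 larger clinics operate 2-3 days per week", and the other 4 are smaller clinics open one day a week.

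**Clinic-level analysis.** Section 9.2 runs this first for most outcomes, "using standard t-tests or, where the observations per clinic vary, t-tests weighted by cluster-size".

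**Individual-level analysis.** Section 9.2 then relies on regression for most analyses and examines significance over a range of assumed ICCs. The Aim 1a logistic model is estimated "using covariates to adjust for baseline characteristics such as age, sex, and physical health". Aim 1b uses model (1): arm, one time coefficient γ, one arm-by-time coefficient δ and a patient random effect, with a vector of patient-level covariates to be added. Of δ it says that it "is the interaction of treatment model with time and shows the intervention effect (task-shifting relative to the control"). Baseline PHQ-9 is offered as a regressor only for the analysis of treated patients.

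**Visits.** Section 7.0: "The client research participants will be assessed at baseline and months 6 and 12".

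**The concern.** A factor balanced by the randomisation no longer adds to the true variance of the arm difference. An unpaired t-test still leaves it in the error term, so the standard error is too large and the test conservative. Weighting by observations per clinic does not remove it. With 10 clinics, and Section 9.1 claiming power only for medium to large effects, this is precision the design has already paid for.

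The second part concerns Aim 1b. Section 9.2 does not say which visit carries the primary arm difference. As the equation is most naturally read, the answer is the raw change to month 12, with baseline PHQ-9 as the first of three outcomes and not as a covariate.

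**Working it through.** **The plan's own figure.** Aim 1b inputs (Section 9.1): SD 3.9, ICC .025, 150 per clinic less 10% attrition = 135, 5 clinics per arm, two-sided α = .05, 80% power.

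(1.960 + 0.842) × 3.9 × √[2(1 + 134 × .025)/(5 × 135)] = 1.24, against 1.26 stated. At ICC .01 and .05 the formula gives 0.91 and 1.65, against .92 and 1.71. These figures are reached without any term for pairs or baseline.

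**Clinic size in the clinic-level t-test.** Assumptions: clinic-mean variance 1; size (3 larger and 2 smaller clinics per arm, so pairs do not cross the size bands) explains a fraction R² of it; two-sided 5% test; effect set to give 80% power at R² = 0. The protocol gives no R².

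- True variance of the arm difference: (2/5)(1 − R²). At R² = .3 this is 0.28.
- Variance that the unadjusted test expects: (2/5)[(1 − R²) + 1.25R²], where 1.25 = 5/4 comes from the n − 1 divisor. At R² = .3 this is 0.43.
- The standard error is therefore too large by √(0.43/0.28) = 1.24.

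Simulation (200,000 trials per cell):

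| R² | Type I, unadjusted (8 df) | Power, unadjusted | Power, size stratum (7 df) | Power, 5 pairs (4 df) |
|---|---|---|---|---|
| 0 | 5% | 80% | 78% | 67% |
| 10% | 4% | 80% | 82% | 72% |
| 30% | 2% | 81% | about 90% | 81% |
| 50% | about 0.5% | 82% | 97% | 91% |

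Type I error is 5% throughout for the stratified and paired tests. Break-even from the noncentrality needed for 80% power (3.20, 3.27 and 3.76 on 8, 7 and 4 df): stratum 1 − (3.20/3.27)² ≈ 4%; pairs 1 − (3.20/3.76)² ≈ 28%.

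R² here refers to clinic-mean variance. At ICC .025 and 135 patients, the between-clinic share of that variance is .025/(.025 + .975/135) = 78%; at ICC .01 it is 58%. If size explains 30% of between-clinic variance, R² is about 23% or 17%.

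**What model (1) estimates.** With t = 0, 1, 2 and complete data, the weights for a slope are (t − 1)/2 = −½, 0, +½; generalised least squares gives the same under compound symmetry and AR(1). Over two periods, δ is the difference in change from baseline to month 12.

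**Baseline adjustment.** Let r be the patient-level correlation between baseline and month 12. Per patient, change has variance 2(1 − r) and baseline adjustment 1 − r², a ratio of (1 + r)/2: .60, .70 and .80 at r = .2, .4 and .6.

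For clinic means, let π be the clinic-level correlation over time. Take ICC .025 (applied here to the score at each visit), 135 patients, r = .4 and unit score variance:

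- Change: 2(.025)(1 − π) + 2(.975)(1 − r)/135.
- Patient-level slope only: .025(1 + r² − 2rπ) + .975(1 − r²)/135.
- Best clinic-level slope: V − C²/V, with V = .025 + .975/135 = .0322 and C = .025π + .975r/135.

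| π | Change | Patient slope (ratio) | Best clinic slope (ratio) |
|---|---|---|---|
| .4 | .0387 | .0271 (.70) | .0271 (.70) |
| .8 | .0187 | .0191 (1.02) | .0160 (.86) |
| .9 | .0137 | .0171 (1.25) | .0122 (.89) |

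The last column treats the slope as known. Estimating it from 10 clinic means beside arm and stratum leaves 7 df for the baseline means and inflates the variance on average by 1 + 1/(7 − 2) = 1.20. The ratios become about .84, 1.03 and 1.07; simulation gives the same.

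**The case against.** **The t-test is not the main analysis.** Section 9.2 itself calls the clinic-level approach low in power and relies on individual-level regression. A reader might infer that those regressions are conservative too. The documents do not support that: their standard errors are not estimated from 10 clinic means, and with an imposed ICC the direction of any error depends on the value chosen. This stands, so the table applies only to the clinic-level test.

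**R² is assumed.** True. At 5–10% the stratum gains 2 points of power or less, and at zero it costs about 2. The case is that the downside is small and the protocol itself gives size as a reason for matching.

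**A SAP could settle this.** The Aim 1a covariate list is open and the covariate vector in model (1) is not itemised, so size could be added. But both are described as patient characteristics, and the t-tests are named without pairing. Baseline PHQ-9 cannot simply join the covariates while it is also an outcome.

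**Model (1) is a recognised form.** It is a difference-in-differences model, and it is defensible where patients are recruited through providers in clinics already working under an assigned model. The protocol also calls t a time period, so visit indicators are not excluded, and with attrition month 6 would carry some information. These points stand: the linear reading is the natural one but not the only one.

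**Month 6.** A reader might infer that model (1) is faulty because a month-6 benefit equalled by month 12 would show as zero. That is no argument for the change proposed here: a month-12 primary contrast would also show zero. What categorical visits add is a separate month-6 estimate.

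**Conclusion.** The point holds in limited form. The randomisation factor is absent from every analysis that Section 9.2 describes, and in the clinic-level t-test this costs power once size explains more than about 4% of clinic-mean variance: roughly 2 points at 10%, 9 at 30% and 15 at 50%. Those figures rest on assumed R² values and on pairs that respect the larger/smaller split. Full pair terms are not the better choice, since they need about 28% to break even.

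For Aim 1b, the firm conclusion is that the primary contrast should be stated outright. The precision argument is weaker. At r = .4 and ICC .025, baseline adjustment saves about 30% of variance if clinic means correlate at .4, and about 10–15% at .8 to .9 with the best clinic-level slope. A reader might infer that adding baseline PHQ-9 always helps; a patient-level covariate alone can lose precision (ratios 1.02 and 1.25), and a clinic-level slope estimated from ten clinics may return nothing when clinics are stable. The protocol gives neither correlation.

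**What to change.** In Section 9.2:

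- Add a larger/smaller clinic-size stratum (6 and 4 clinics) to the clinic-level tests and to the Aim 1a and Aim 1b regressions. Keep the 4-df paired test as a sensitivity analysis only.
- For Aim 1b, write visit as categorical, name the month-12 arm difference as the primary contrast and report month 6 beside it.
- Adjust for baseline PHQ-9 at both patient and clinic-mean level, and report the unadjusted change difference alongside, because the gain cannot be known in advance.

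Cost: rewording and no new data. In a 10-clinic analysis the stratum and the clinic-mean baseline take one degree of freedom each (8 to 6), and the clinic-level slope adds its own estimation error as shown above. If only one change is made, the size stratum is the cheaper and safer one.

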## 1.0 INTRODUCTION

In response to the NIH/PEPFAR RFA for implementation science and impact evaluation, this proposal addresses these priority areas: integration of HIV primary care and a common co-morbidity (depression), and examining depression treatment as a means to promote HIV care adherence and prevention of transmission. Sub-Saharan Africa (SSA) has undergone dramatic scale-up of HIV care and antiretroviral therapy (ART), with over 3 million on treatment in the region. The ultimate goal of HIV care is not only prolonged health and survival, but to provide a functioning level that enables clients to work, provide for their families, and prevent transmission of the virus to others. In fact, ART has led to dramatic reductions in mortality and morbidity, reduced infectiousness, and increased work productivity. However, our research in Uganda reveals depression to be a key threat to these critical public health benefits of HIV treatment. In our prospective cohort study that observed clients over the first year of care, multivariate analysis revealed depression to be the key impediment to ART adherence, whether or not someone was able to work, and consistent condom use.

As in other parts of the world, roughly half of all persons living with HIV/AIDS (PLHA) in SSA have elevated depressive symptoms, and 20-30% have clinical depression. Despite this high prevalence, and the public health consequences of depression, mental health care is rarely integrated into HIV care programs, including those supported by PEPFAR; hence, depression is rarely diagnosed and treated. Antidepressants are effective in treating depression in PLHA, including in SSA as shown by our current research in Uganda, and inexpensive; however, the lack of trained mental health specialists is a major barrier to provision of treatment. Under current models of care, increased emphasis on depression treatment would fall in the hands of primary care physicians, and with most clinics having 1 or 2 physicians for seeing 100-200 patients daily, many depressed patients would likely still go undetected and bottlenecks of patients waiting for physicians would worsen. Task-shifting approaches in which nurses and other cadres take on tasks normally conducted by physicians have been used successfully in SSA in efforts to sustain ART scale-up, but not with regard to mental health treatment. Algorithm-based, nurse-driven management of antidepressant treatment has been shown to be effective with non-HIV patients in the U.S. and in developing countries, but has not been studied with PLHA or in SSA.

**INDEPTH (INtegration of DEpression Treatment in HIV care) Uganda** is a cluster randomized trial that attempts to identify an effective, resource-efficient model for integrating depression treatment into HIV care in low resources settings such as Uganda. In the HIV clinics of 10 healthcare facilities, the trial is comparing two active task-shifting implementation models of depression care: a *protocolized model* in which care is provided largely by trained nurses who act as depression care managers, and a model that relies on the *clinical acumen* of trained primary care providers (most, but not all, of whom are nurses as well). An alternative approach to the use of a structured protocol to guide depression care by non-mental health professionals, the clinical acumen model (like the protocolized model) takes an active approach to depression care by integrating a brief routine depression screening process for all patients at each clinic visit, but what the primary care provider does with this screening information is up to their discretion as opposed to following a structured protocol. So both of these models are active task-shifting models of depression care, as the clinical acumen model goes beyond current usual care, which relies solely on primary care provider to assess and treat, or refer to external specialists—which has resulted in depression being severely under-diagnosed and treated.

